#### 2.1.1 Sample size

As this study is a randomized controlled trial, the respondents will be divided into manual intervention group, artificial intelligence (AI) intervention group, artificial intelligence and manual combined intervention group, and observe the BMI of pregnant women, maternal weight and maternal adverse pregnancy outcomes as the main outcome indicators. The sample size was calculated based on an expected effect size of 0.5, which corresponds to the minimal clinically important difference (MCID) of the primary outcome. This MCID was determined based on previous literature and clinical judgment. Setting bilateral α = 0.05, the degree of certainty was 90%. Using the PASS15 software, we obtained a sample size of N1 = 40 cases for the group and N2 = 40 cases for the group and N3 = 40 cases for the group. For a total of at least 120 subjects to be included in the study.

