##### 2.1.2.2 Exclusion and withdrawal criteria

The following exclusion criteria were applied to the patient samples in this study: pregnancies resulting from assisted reproductive technology; individuals on bed rest; patients with a diagnosis of diabetes mellitus or gestational diabetes mellitus; those with uncontrolled hypertension; individuals with a recent diagnosis of thyroid disease within the preceding 30 days; subjects with a history of cardiovascular, oncological, pulmonary, or severe gastrointestinal diseases; participants with a history of eating disorders or bariatric surgery; individuals with serious mental illnesses; those with a recent history of mood or anxiety disorders; patients with substance abuse or alcohol use disorders; pregnancies beyond 13 weeks of gestation.

Additionally, the following samples were excluded from the study: participants who withdrew from the study; individuals experiencing severe acute diseases requiring treatment during the study period.

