#### 2.7.2 Research implementation phase

The study will rigorously enforce the inclusion criteria for survey subjects, ensuring a meticulous selection and inclusion process into the study cohort. Participants with obesity pregnant women and their families will receive brochures detailing the prevention and treatment of chronic diseases, and informed consent will be obtained to ensure the authenticity of the feedback and to maintain a high response rate. Reminders will be sent via phone calls or text messages to minimize loss to follow-up during the survey process. Surveyors are committed to upholding principles of objectivity and equality, introducing the study's purpose and significance to each participant prior to commencing the survey and obtaining their informed consent. Furthermore, to ensure data integrity, the survey questionnaires will undergo regular review by auditors, with any inconsistencies or issues being addressed through immediate verification and correction.

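### The calculated 40 per arm is also the enrolment floor, with no allowance for loss, while women who leave after entry are excluded; a trial that stops at 120 does not deliver the 90% power it states

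*Protocol article*

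**What the plan says.** Section 2.1.1 gives the whole chain from assumptions to total. The effect: "The sample size was calculated based on an expected effect size of 0.5, which corresponds to the minimal clinically important difference (MCID". The error rates: "Setting bilateral α = 0.05, the degree of certainty was 90" per cent, which I read as 90% power. The result: "we obtained a sample size of N1 = 40 cases for the group and N2 = 40 cases for the group", with the same number for the third arm. The recruitment figure follows at once: "For a total of at least 120 subjects to be included in the study". No loss rate or inflation step stands between the result and the total, and the text does not say that 40 already contains an allowance.

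Section 2.1.2.2, after the entry criteria, lists further samples as excluded from the study: "participants who withdrew from the study; individuals experiencing severe acute diseases requiring treatment during the study period". Both conditions can arise only after entry.

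Section 2.7.2 treats loss as something to be managed: "Reminders will be sent via phone calls or text messages to minimize loss to follow-up during the survey process". It gives no rate.

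Women enter at 8 to 12 weeks of gestation (section 2.1.2.1) and are seen at about 20, 28 and 36 weeks and again postpartum (section 2.1). Section 2.4.1 offers repeated-measures ANOVA or mixed-effects models for the primary outcomes. Section 2.6 names generalized estimating equations (GEE) as the main analysis.

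**The concern.** A power calculation returns the number of women whose data must enter the analysis. The plan uses that number as the least it will enrol, and it also has a rule that takes enrolled women out. Both statements can hold only if nobody withdraws and nobody develops severe acute disease between early pregnancy and the postpartum visit.

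A trial that closes at its stated minimum would therefore carry a 90% figure that belongs to a larger analysed set than it has. A null comparison between arms would be read against that figure. The gap would be widest at the late visits, on which the article's third sub-question (short-, medium- and long-term effects) depends.

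This is a separate question from whether 40 analysed women per arm give 90% power at all. Correcting that calculation would not by itself add an allowance for loss.

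**Working it through.** **Inputs.** From section 2.1.1: two-sided α = 0.05, power 90%, effect size 0.5 (scale, SD, test and comparison not given), 40 per arm, total at least 120. The loss rate is not in the documents. I assume 10% to 20% for the main statement and show 25% as well.

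**Step 1: the plan's own figures.** 3 × 40 = 120, so the total is the uninflated result.

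The 40 itself does not follow from the printed inputs on the plain readings:
- Two-sample comparison with standardised difference d = 0.5: n = 2 × ((1.960 + 1.282)/0.5)² ≈ 84.1, so 85 per arm.
- Three-group ANOVA with f = 0.5: 18 per arm.

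Because the 40 is not reproduced, I show the effect of loss in two ways: granting the plan its 90% at 40 per arm, and taking the printed 0.5 as d.

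**Step 2: effect that would justify the claim.** For a pairwise two-sided t test with n per arm, the noncentrality is d × √(n/2) with 2n − 2 degrees of freedom. Solving for 90% at n = 40 gives d = 0.734 (noncentrality 0.734 × √20 = 3.28, 78 degrees of freedom). This value is back-solved and appears nowhere in the article.

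**Step 3: power when only 120 are enrolled and lost women contribute nothing.** Analysed n = 40 × (1 − loss).

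| Assumed loss | Analysed per arm | Power, d = 0.734 | Power, d = 0.5 |
|---|---|---|---|
| 0% | 40 | 90.0% | 59.8% |
| 10% | 36 | 86.7% | 55.3% |
| 15% | 34 | 84.7% | 52.9% |
| 20% | 32 | 82.4% | 50.4% |
| 25% | 30 | 79.8% | 47.8% |

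**Step 4: does the choice of test matter?** A three-group ANOVA set to 90% at 40 per arm (f = 0.329) gives 86.4%, 84.2%, 81.8% and 79.0% at 36, 34, 32 and 30 per arm. The pattern is the same.

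**Step 5: what an allowance would have looked like.** To keep 40 analysed, enrolment is 40/(1 − loss). At 10% this is 44.4, so 45 per arm and 135 in total. At 20% it is 50 per arm and 150 in total. The stated floor lies below both.

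**Limit of the calculation.** Step 3 removes a lost woman completely. That matches the section 2.1.2.2 exclusion as worded. It does not describe a woman who misses a visit or delivers before 36 weeks: her earlier measurements would still enter a GEE or mixed model.

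**The case against.** Five points can be made for the plan.

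- **At least 120 is a floor.** The sponsor may enrol more, so it cannot be said that the power will fall short. This stands, and the point is conditional for that reason. But no larger target is fixed, and a trial that stops at 120 complies with the plan.
- **The article is a condensation, and its flowchart is not shown.** An allowance could sit elsewhere. That is possible, but section 2.1.1 prints every step through to a total, and that total is exactly three times the calculated number. The exclusion of withdrawn women is also stated, not merely left out.
- **The planned analysis uses partial data.** GEE or a mixed model keeps the visits that were made, and section 2.1.2.2 says nothing about missed visits or early delivery. This stands. The table overstates the fall for such women, and a reader should not infer that delivery before 36 weeks removes a woman from the analysis. It does not rescue the women who withdraw or fall severely ill, because they are excluded outright.
- **The 0.734 is invented and 40 cannot be reproduced.** Both are true. If 0.5 were ANOVA f, only 18 per arm would be needed and moderate loss would leave power above 90%. But 40 would then not be the calculated result, and f is an odd scale for a minimal clinically important difference. The unexplained 40 is the larger problem and must be settled first.
- **The retention reminders are routine.** Agreed: they show that loss is foreseen, not how much.

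**Conclusion.** The point holds in conditional form. The plan equates the analysed number with the enrolment floor and excludes women who leave after entry. If recruitment stops at 120 and any woman is excluded in this way, the analysed number is below 40 in at least one arm. The 90% is then not met on the plan's own premise that 40 analysed per arm gives it.

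The size depends on an assumed loss rate and on complete removal of lost women. On the effect that would justify the claim, the shortfall is about 3 to 8 percentage points at 10% to 20% loss (90.0 − 86.7 = 3.3; 90.0 − 82.4 = 7.6). On the printed 0.5 read as d, it is about 4 to 9 points from a base that is already near 60% (59.8 − 55.3 = 4.5; 59.8 − 50.4 = 9.4). The fall is smaller wherever partial data are kept.

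A reader might infer more: that the trial is bound to miss its power, or that the total is miscalculated. The documents support neither. The floor permits more enrolment, no loss rate is given, and 3 × 40 is 120. The defect is a missing design assumption combined with an exclusion rule that makes it matter. It should be corrected, but it does not by itself invalidate the trial.

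**What to change.** 1. **Section 2.1.1.** State whether 120 is the number randomised or the number analysed. Give the assumed loss at the time point of the primary comparison, and restate the power for the number then analysable (34 per arm if, for example, 15% is assumed). Do this only after the effect size, its scale and the test behind 40 per arm have been corrected. Until then the restated figure could be anything from 84.7% to 52.9% at the same 15% loss.
2. **Section 2.1.2.2.** Replace the exclusion of women who withdraw or develop severe acute disease with an analysis rule: all randomised women are analysed in their assigned group, using every measurement collected before they leave. Without this change, keeping pre-withdrawal data contradicts the text. The rule concerns the analysis set only.
3. **Sections 2.4.1 and 2.6.** Reconcile the two by naming the mixed-effects model as the main analysis for weight and BMI. At present it is only one of two options in 2.4.1, and 2.6 makes GEE the main analysis. A correctly specified mixed model stays valid when dropout depends on observed values; unweighted GEE generally does not.

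The cost is some rewording and a less favourable printed power. No extra participants are needed.

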#### 2.1.2 Recruitment

In this study, the selection of participants will follow the steps outlined as follows.

##### 2.1.2.1 Eligibility and inclusion criteria

In this study, pregnant women were initially identified within the electronic health record system based on the following eligibility criteria: aged 18 years or older; carrying a singleton pregnancy between 8 to 12 weeks of gestation; with a pre-pregnancy body mass index (BMI) of 28.0 kg/m^2^ or higher; possessing clear awareness and capability to understand and fulfill the study objectives and follow-up requirements; having access to a telephone, or being reachable via a family telephone for follow-up purposes; and being proficient in Mandarin, as subsequent interventions are conducted in Mandarin.

##### 2.1.2.2 Exclusion and withdrawal criteria

The following exclusion criteria were applied to the patient samples in this study: pregnancies resulting from assisted reproductive technology; individuals on bed rest; patients with a diagnosis of diabetes mellitus or gestational diabetes mellitus; those with uncontrolled hypertension; individuals with a recent diagnosis of thyroid disease within the preceding 30 days; subjects with a history of cardiovascular, oncological, pulmonary, or severe gastrointestinal diseases; participants with a history of eating disorders or bariatric surgery; individuals with serious mental illnesses; those with a recent history of mood or anxiety disorders; patients with substance abuse or alcohol use disorders; pregnancies beyond 13 weeks of gestation.

Additionally, the following samples were excluded from the study: participants who withdrew from the study; individuals experiencing severe acute diseases requiring treatment during the study period.

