## 1 Introduction

Obesity is an abnormal or excessive fat accumulation that can impair health. A research study shows that the total number of obese children, adolescents and adults worldwide by 2022 has exceeded 1 billion, of which 879 million are adults. Since 1990, obesity rates among adults have more than doubled among women (1). In China, the problem of overweight and obesity among residents is increasingly prominent, and the rate of overweight and obesity among all age groups in urban and rural residents continues to rise, and more than half of adult residents are overweight or obese. Obesity is not only an independent health problem, but also an important risk factor for multiple chronic diseases such as type 2 diabetes, cardiovascular disease, hypertension, and so on (1, 2). Obesity often coexists with other chronic diseases, creating a complex network that complicates treatment and management. Furthermore, obesity is linked to several biological mechanisms, such as inflammation, oxidative stress, and endocrine disorders, which may collectively contribute to the development of chronic diseases (3). With the increasing rate of obesity worldwide, the incidence of chronic diseases increases, placing a substantial burden on individual health, healthcare systems and socioeconomic (4).

Maternal obesity is associated with a range of adverse pregnancy outcomes, including gestational diabetes mellitus, gestational hypertension, preeclampsia, need for cesarean delivery, and large for gestational age (5–8). These complications not only affect the health of the mother during pregnancy but may also have long-term consequences for the child, such as increased risk of prematurity, large for gestational age, birth-related trauma, hypoglycaemia, neonatal intensive care unit admission, stillbirth, increased risk of obesity and metabolic disorders in later life (8–11).

According to the study, obese patients had 46% more hospitalization, 27% more clinic and outpatient costs and 80% more prescription drugs compared with normal weight individuals (12). In recent years, several guidelines and expert consensus on obesity and chronic diseases have been published at home and abroad, but most of them are suggestions for evaluation methods or diagnosis and treatment procedures, and lack systematic prevention and management countermeasures. Therefore, it is important to study effective strategies for chronic obesity intervention to improve public health.

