### 2.2 Randomization

After recruitment, the research team will conduct a pre-enrollment assessment and post-enrollment informed consent with the participants and their families, followed by randomization grouping:

A comprehensive assessment will be conducted before the participants are enrolled, including structured questionnaires and clinical examinations.

The approved subjects were randomly divided into Manual intervention group, artificial intelligence intervention group (AI intervention group), artificial intelligence and artificial combined intervention group (AI & Manual intervention group). The specific randomization operation is as follows: This study uses a simple randomization method. Random number series were randomly generated by the study designer using the RANDBETWEEN formula in EXCEL. The project will divide the subjects into different groups according to the sequence, the intervention team will know the grouping results, and the subjects will not know the grouping results.

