### 2.4 Outcomes

#### 2.4.1 Primary outcomes

The primary outcomes of the study include maternal body mass index (BMI), maternal weight, and adverse pregnancy outcomes. The primary outcome measures (such as BMI, maternal weight, and adverse pregnancy outcomes) will be assessed using Repeated Measures ANOVA or Mixed Effects Models to evaluate the intervention effects. For long-term effect analysis, Generalized Estimating Equations (GEE) or Cox Proportional Hazards Models will be employed to assess the short-term, medium-term, and long-term impacts of the interventions. Cost-effectiveness analysis will be conducted using Quality-Adjusted Life Years (QALY) and Incremental Cost-Effectiveness Ratios (ICER) to evaluate the economic efficiency of different intervention measures, with sensitivity analysis performed to verify the robustness of the results.

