### 2.6 Statistical analysis

Participants' socio-demographics are presented as count and proportion, and the χ^2^ test was used to assess categorical variables. The continuous variables normally distributed were assessed by the student's *t*-test. The Fisher's exact or the chi-square test was adopted for categorical data, and statistical significance was set at *p* < 0.05. The main analysis was performed using generalized estimating equations (GEE) model. The GEE solved the problem of correlation of longitudinal data, utilizing the results of each measurement in the longitudinal data, which greatly reduces the loss of information (20). To clarify whether socioeconomic status affects the effectiveness of ILSM, we conducted several subgroup analyses for physiological health outcomes and health behaviors, and added the interaction terms to generalized estimating equations model to assess the interactions between time (at baseline, 3-month, 6-month, and 18-month) and group (intervention and control). We also used GEE to analyze the health benefits of intervention and control groups among participants with different socioeconomic status. Significance level of the associations in the final model was set at *P*-value 0.05. The data were analyzed using SPSS 20.0 (IBM Corporation, Armonk, NY, USA).

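### Read literally, section 2.1.2.2 removes randomised women who withdraw or become severely ill, which breaks the randomised comparison and may remove primary-outcome events

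*Protocol article*

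**What the plan says.** Section 2.1.2.2 of the protocol article first lists baseline exclusion criteria. A separate sentence then adds two further groups as excluded from the study: "participants who withdrew from the study; individuals experiencing severe acute diseases requiring treatment during the study period".

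Four other places bear on this:

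- **Timing.** Section 2.2 describes "pre-enrollment assessment and post-enrollment informed consent with the participants and their families, followed by randomization grouping". Section 2.1 schedules follow-up visits through pregnancy and up to 3 months postpartum.
- **Primary outcomes.** Section 2.4.1 states: "The primary outcomes of the study include maternal body mass index (BMI), maternal weight, and adverse pregnancy outcomes". It does not list the components of the last of these. The Introduction names adverse pregnancy outcomes linked to maternal obesity, "including gestational diabetes mellitus, gestational hypertension, preeclampsia, need for cesarean delivery, and large for gestational age".
- **Analysis.** Section 2.6 states: "The main analysis was performed using generalized estimating equations (GEE) model". It justifies the method as "utilizing the results of each measurement in the longitudinal data, which greatly reduces the loss of information".
- **Knowledge of allocation.** Section 2.2 says that the intervention team knows the group assignment.

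**The concern.** Neither condition works as a screening criterion. Withdrawal from the study, and illness while it is running, happen for the most part after a woman has been allocated. Removing women at that stage gives up the protection of randomisation.

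Both conditions can plausibly differ by arm. The three arms deliver a demanding diet, fasting and exercise programme through different providers, so the reasons for leaving need not be the same in each. Both can also be related to outcome. A woman who leaves may be one whose weight is going badly, and a severe acute illness in pregnancy may itself be an adverse pregnancy outcome. The term for severe illness is not defined, and a team that knows the allocation could influence how it is applied.

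At stake are the between-arm contrasts on all three primary outcomes, and the visibility of harm if severe illness leads to removal from the data rather than to a recorded event.

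**Working it through.** **The passages side by side.** Randomisation follows assessment and consent (section 2.2), and the study period extends to 3 months postpartum (section 2.1). The two added conditions therefore fall largely after allocation. No section says that excluded women stay in the analysis, that data up to withdrawal are kept, or that analysis is by assigned group. Section 2.6 chooses GEE so that every measurement contributes; removing whole women discards measurements already taken. The two statements pull in opposite directions.

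**Plan's own figure.** There is none to reproduce: the article gives no expected rate of withdrawal or exclusion. All rates below are assumptions. Only the 40 women per group and the effect size of 0.5 come from the article (section 2.1.1).

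**Adverse outcomes.** Let the true risk be r in both arms, the share of women dropped d, and the share of dropped women who had an event e. The observed risk among those retained is (r − d·e)/(1 − d). Take r = 0.30, d = 0.10 in arm A and d = 0.05 in arm B.

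| e | Arm A | Arm B | False difference |
|---|---|---|---|
| 0.30 (same risk as the rest) | (0.30 − 0.03)/0.90 = 30.0% | (0.30 − 0.015)/0.95 = 30.0% | 0 |
| 0.50 | (0.30 − 0.05)/0.90 = 27.8% | (0.30 − 0.025)/0.95 = 28.9% | about 1 point |
| 1.00 | (0.30 − 0.10)/0.90 = 22.2% | (0.30 − 0.05)/0.95 = 26.3% | about 4 points |

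In counts, for the last row with 40 per arm: each arm has 12 events. Arm A loses 4 women, all with events, leaving 8 of 36. Arm B loses 2, leaving 10 of 38. Where a false difference appears in the table, it favours the arm that lost more women.

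If dropping is equal in both arms, there is no false difference, but events are still lost. For example, removing 20% of the women with events in each arm turns 30% into 0.30 × 0.80/(1 − 0.30 × 0.20) = 25.5%.

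**Weight.** Assume that 20% are dropped in one arm and 10% in the other, and that dropped women are 0.75 SD worse. The result depends on what they are worse than.

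- Worse than the mean of all randomised women in the arm: the retained mean shifts by p/(1 − p) × 0.75. That is 0.25 × 0.75 = 0.1875 SD and 0.111 × 0.75 = 0.083 SD, a bias of 0.104 SD.
- Worse than the mean of retained women: the shift is p × 0.75. That is 0.150 SD and 0.075 SD, a bias of 0.075 SD.

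Against an effect of 0.5 this is 0.075/0.5 = 15% to 0.104/0.5 = 21%, but only if 0.5 is in SD units; section 2.1.1 does not state the metric.

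**The case against.** The sentence stands under a heading that also covers withdrawal, within the recruitment section and not the statistical one. It can be read as saying who leaves the study, not whose data are deleted. Section 2.6 names no completer set, its reason for GEE fits keeping data up to withdrawal, and analysis sets are commonly left to an analysis plan that is not shown. This stands as far as intent goes: that the analysed set will consist of women who completed and stayed well is an inference. It does not rescue the wording. The sentence says these women were excluded from the study, and an analysis plan that kept them would have to contradict it.

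Three stronger readings are tempting and are not supported.

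- **That the rule certainly deletes primary-outcome events.** Section 2.4.1 lists no components, the severe illnesses are undefined, and the Introduction's list is background, not an endpoint definition. The rule might be meant only for illness unrelated to pregnancy. Still, pre-eclampsia is on the article's own list and a severe case fits the wording, so removal of events is possible.
- **That women who develop gestational diabetes during follow-up are also removed.** That condition is in the first list, which also excludes pregnancies past 13 weeks. Applied during follow-up, that criterion would remove everyone by the 20-week visit, so the list can only be a baseline screen.
- **That the bias is 4 points or 0.10 SD.** These are the upper ends of the illustrations above. The 4 points require every dropped woman to be an event, and twice as many women dropped in one arm at equal true risk.

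**Conclusion.** Wrong as written. The article states a rule that, followed literally, takes randomised women out of the study for reasons arising largely after allocation, and nothing else in the article reverses it. This is a stated rule, not a detail left to another document. The conclusion that it breaks the randomised comparison rests on the text and needs no figure.

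The size does depend on assumptions. In the scenarios shown it runs from zero to about 4 percentage points for adverse outcomes and from about 0.075 to 0.10 SD for weight. Equal exclusion of similar women would leave no false difference, though precision and events would still be lost. Loss of primary-outcome events is a well-supported possibility and not an established fact. Recruiting more women would restore precision but would not remove the selection.

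**What to change.** Change the analysis and data-retention wording only; any clinical rule for stopping the programme stays as it is.

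- Separate stopping the intervention from leaving the analysis.
- Analyse every randomised woman in her assigned arm.
- Keep all measurements up to withdrawal in the longitudinal model.
- Take delivery outcomes from the medical record unless consent for record use is withdrawn. Table 1 already names the medical record as a source for health status.
- Count a severe acute pregnancy illness as an outcome or adverse event in the analysis.
- Report withdrawals, with reasons, by arm.
- Keep the completer set as a sensitivity analysis only.

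The cost is revised wording and a little more record abstraction for women who stop the programme. The change should come early, because outcomes not collected after withdrawal may not be recoverable.
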